# A group- and smartphone-based psychological intervention to increase and maintain physical activity in patients with musculoskeletal conditions: study protocol for a randomized controlled trial (“MoVo-App”)

**DOI:** 10.1186/s13063-020-04438-4

**Published:** 2020-06-08

**Keywords:** Blended intervention, App, Motivation and volition, Psychological intervention, Long term, Exercise, Sport activity, Orthopedic rehabilitation, Randomized controlled trial

## Abstract

**Abstract:**

**Background:**

Interventions designed to increase the level of physical activity are crucial in the treatment of patients with musculoskeletal conditions. The psychological group-based intervention MoVo-LISA based on the Motivation-Volition (MoVo) Process Model has been shown to effectively promote physical activity. The aim of this study is to evaluate whether a MoVo-based app (MoVo-App) subsequent to MoVo-LISA during orthopedic inpatient care can support people to increase and maintain their amount of physical activity.

**Methods/design:**

In this parallel-group randomized controlled trial, patients with musculoskeletal disorders will be randomized to either (a) a combination of the group-based intervention program MoVo-LISA to promote physical activity plus the MoVo-App or (b) the group-based intervention program alone without the app. The intervention group will receive the MoVo-App after discharge from inpatient rehabilitation. They receive help to increase and maintain their level of physical activity (initiated by the group program) by tracking their health goals, activity plans, major barriers, and barrier management that were developed during the group-based program. We will recruit 224 initially minimally active participants during orthopedic rehabilitation care. Outcomes are assessed at clinic admission; discharge; 6 weeks; and 3 (post-treatment), 6, and 12 months after discharge (follow-up). The primary outcome is sport activity (active/inactive and minutes of activity) at 6-month follow-up. Secondary outcomes are movement activity, cognitive mediators of behavioral change (e.g., self-efficacy, action planning), and health-related variables (e.g., pain intensity, depression). To evaluate intervention effects, linear mixed effects models (both on intention-to-treat basis with an additional per-protocol analysis) will be conducted with each outcome variable and with time as the within-subjects factor and group as the between-subjects factor, along with all two-way interactions and accounting for covariates as fixed effects.

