Can the combination of the face-to-face group-based intervention MoVo-LISA and MoVo-App increase maintenance of the initiated physical activity level in patients with musculoskeletal disorders more than MoVo-LISA without subsequent MoVo-App use?

We hypothesize that the additional MoVo-App can help to maintain the initiated level of physical activity (by the face-to-face group program) 6 months after clinic discharge in patients with musculoskeletal disorders more than MoVo-LISA without the app.

The following are secondary research questions:
2.Can the combination of MoVo-LISA and MoVo-App improve cognitive mediators of behavioral change (e.g., self-efficacy or action planning), and health-related variables (e.g., pain intensity, depression) in patients with musculoskeletal disorders more than the same face-to-face group-based intervention without subsequent MoVo-App use?3.Which cognitive and sociodemographic factors moderate and mediate the effects of MoVo-LISA and MoVo-App?

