### Proposed sample size/power calculations

In a previous group-based MoVo-LISA trial with orthopedic patients, exercise duration was 156 min/week immediately after the intervention, which decreased to 92 min/week at 6 months after discharge [16]. If the MoVo-App is able to stabilize the post-treatment effect, a medium effect size of (standardized mean difference) *d* = 0.62 for the main effect and a small to medium effect size for the interaction effect group (MoVo-LISA + MoVo-App) × time of *d* = 0.35 at the 6-month follow-up (T4) can be expected. However, the effect size estimate for the interaction effect could only be extrapolated from interaction effects observed for group trials comparing MoVo-LISA with a wait-list control group [19]. We assume a baseline measure of the outcome to be used as a covariate and a correlation between pre- and postmeasures of 0.33 based on prior data. With a power of 80%, a significance level of 5%, and small to moderate effect sizes, and considering an estimated dropout rate of 15%, a total sample size of 224 is required.

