### Primary outcome

The level of sport activity in minutes per week is measured with the BSA-F [51]. This is a validated German self-report instrument used to measure the level of movement activities (functional physical activities of daily living; *see* “Secondary outcomes” section below) and sport activities (sport- and health-related exercises, such as soccer, jogging, Nordic walking, Pilates, or fitness training) in minutes per week. For the sport activity subscale, the participants list a maximum of three sport activities in which they have engaged within the last 4 weeks. For each activity episode, participants indicate the frequency and duration in minutes. Activities that do not target larger groups of skeletal muscles and do not lead to maintenance of or increases in endurance, power, coordination, or flexibility are classified as invalid activities for this group. For each valid activity, an activity amount in minutes per week is calculated by multiplying frequency and duration divided by 4. All single amounts of the named sport activities are added to obtain the individual’s score on the Sport Activity Index. The validity of the BSA-F has been shown in several studies. However, data do not permit an analysis of the reliability of the instrument [51].

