### Statistical analyses

The primary outcome of physical activity assessed with the respective subscale of the BSA-F at T4 (post-treatment of MoVo-App) will be analyzed as a dependent variable and its baseline value as a covariate, adjusted for sex and age and potentially other covariates. Continuous secondary outcomes will be analyzed accordingly. The statistical analysis for all research questions will be based on linear mixed-effects models with restricted maximum likelihood estimation to account for missing data [71]. The model is a mixture model, thus assuming two distinct distributions: (1) a binomial model (patients becoming physically active from inactivity and vice versa) and (2) a Gaussian distribution of minutes of physical activity per week for those being physically active. In the linear mixed-effects models, time (T1 to T5) will be the within-subjects factor, and intervention (MoVo-LISA and TAU plus MoVo-App vs. MoVo-LISA and TAU) will be the between-subjects factor. All two-way interactions will be considered. Main effects and interactions will be estimated for time points T3 to T5.

Baseline minutes of sport activity, age, sex, and body mass index will be included as covariates, along with other relevant demographic and clinical characteristics (e.g., disease, pain intensity, pain interference) collected through patient self-report. The model will allow for random intercepts, and all other factors will be treated as fixed effects. All statistical analyses will be performed using R software [72].

We expect to see a skewed distribution in our primary outcome physical activity, and, following guidance [72, 73], we will use transformations or consider using generalized or mixture-distribution mixed models [72]. Effects will be considered significant if *p* < 0.05. Assumptions for general, generalized, or mixture-distribution models will be checked graphically and with tests appropriate to the model [74, 75]. In addition, we will run several model checks by comparing increasingly complex models with different covariance structures, link functions, and estimation procedures with a null model via likelihood ratio tests and comparison of fit via the Akaike information criterion and Schwartz’s Bayesian information criterion [76].

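### The article fixes 6 months (T4) as the primary time point but contradicts itself on which outcome component and which effect is tested there

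*Protocol article*

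**What the plan says.** **Time point.** The abstract, the hypothesis in the Background and the sample size section all point to 6 months after discharge (T4). The hypothesis is that the app "can help to maintain the initiated level of physical activity (by the face-to-face group program) 6 months after clinic discharge".

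**Outcome.** The abstract's Methods/design paragraph says: "The primary outcome is sport activity (active/inactive and minutes of activity) at 6-month follow-up". The Primary outcome section names only one quantity: "The level of sport activity in minutes per week is measured with the BSA-F". The Statistical analyses section models two parts: a binomial part for moving between inactive and active, and a Gaussian part for weekly minutes among active patients.

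**Effect.** The Statistical analyses section opens with the T4 value as dependent variable and its baseline as covariate. It then says "time (T1 to T5) will be the within-subjects factor", takes in all two-way interactions, and adds: "Main effects and interactions will be estimated for time points T3 to T5". The decision rule is general: "Effects will be considered significant if" p < 0.05.

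**Sample size.** The calculation gives d = 0.62 for the main effect and "a small to medium effect size for the interaction effect group" by time, d = 0.35 at T4. It then refers to small to moderate effect sizes together and arrives at 224.

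**Model form.** The model is said to be a mixture model. Later, transformations or generalized or mixture models are to be used or considered, with checks "comparing increasingly complex models with different covariance structures, link functions, and estimation procedures with a null model via likelihood ratio tests" and information criteria.

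**The concern.** A confirmatory trial needs a reader to be able to say beforehand which single result answers the primary question. Here three things are open at T4.

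- **Component:** active/inactive, minutes, either, or both.
- **Effect:** the baseline-adjusted T4 difference, a group main effect, or a group-by-time interaction. These are different estimands with different power.
- **Model:** the distribution, link and transformation may be settled after the data have been seen.

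With p < 0.05 for every effect and no order among them, a favourable result on one component could be reported as the primary finding while the other shows nothing. Separately, a difference in minutes among active patients only can mislead. If the app brings otherwise inactive patients to a low level of activity, they enter the active subset with few minutes. The mean among active patients can then fall even though the mean over everyone randomised rises.

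**Working it through.** **Inputs.** From the sample size section: d = 0.35 (interaction at T4), d = 0.62 (main effect), pre-post correlation r = 0.33, power 80%, significance level 5%, dropout 15%, N = 224. From the Study design section: 1:1 allocation. Sidedness is not stated; two-sided is assumed.

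**Step 1: which effect does 224 serve?** Completers per arm for a baseline-adjusted difference are n = 2 × (1.960 + 0.842)² / d² × (1 − r²), with 1 − r² = 0.891.

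| Target | Per arm | Completers | Divided by 0.85 |
|---|---|---|---|
| d = 0.35, baseline-adjusted | 115 | 230 | 271 |
| d = 0.62, baseline-adjusted | 37 | 74 | 88 |
| d = 0.35, difference in change, factor 2(1 − r) = 1.34 | 172 | 344 | 405 |

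None of these gives 224 with dropout included. The nearest is 230, which leaves dropout out. A match by the first formula needs d of about 0.38: 194 completers, which becomes 229 when divided by 0.85 or 224 when multiplied by 1.15. The stated N therefore does not reveal which effect was meant.

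**Step 2: false positives at T4 from two components.** Each is tested at 5% and either counts as success.

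- Independent tests (assumed): 1 − 0.95² = 0.0975.
- Upper bound under any dependence: 2 × 0.05 = 0.10.
- Lower limit, if the two tests always agree: 0.05.

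**Step 3: power with 224 randomised.** Completers: 224 × 0.85 = 190.4, so 95 per arm; √(95/2) = 6.892.

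- Adjusted T4 difference, d = 0.35: 0.35 / √0.891 × 6.892 = 2.56; 2.56 − 1.96 = 0.60; power 72%.
- The same at 2.5% (first step of Holm with two components): 2.56 − 2.24 = 0.31; power 62%.
- The same at 5% with d = 0.62: power above 99%.
- T1-to-T4 group-by-time contrast, d = 0.35 on the raw SD: 0.35 / √1.34 × 6.892 = 2.08; power 55%.
- The same contrast with d on the change-score SD: 0.35 × 6.892 = 2.41; power 67%.

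The documents give no standardiser for d = 0.35. The last two lines also borrow r = 0.33 as the T1–T4 correlation. They show that the choice of effect matters; they do not give the trial's actual power.

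**Step 4: what the Gaussian part compares.** The Primary outcome section adds up the minutes of all valid activities, so a patient with no valid activity has an index of zero and belongs in a comparison of that index. The Gaussian part leaves such patients out, and being active at T4 is itself something the app is meant to change. That part therefore estimates a difference between subsets formed after randomisation, not the difference in the index between the randomised groups.

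**The case against.** The strongest defence has four parts.

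**The recommended analysis is already there.** The Statistical analyses section does open with the T4 value adjusted for baseline. That stands, but the same section then adds main effects, interactions and a two-part model under one significance rule, and never says the opening analysis decides.

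**A two-part model is a recognised way to handle many zeros, and both parts come from one index.** True. It still yields two group effects, and no rule says how they combine into one answer.

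**Multiplicity rules may sit in an analysis plan that is not shown.** A missing rule alone would be no finding. The conflict between the abstract and the Primary outcome section, and the two effect sizes behind one N, are in the article itself.

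**The likelihood-ratio and information-criterion comparisons are described as model checks.** This is fair, so the point is only that the article first states a mixture model and then leaves transformation, generalized or mixture form open.

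Two stronger readings are tempting but not supported. A reader might infer that T3, T4 and T5 are all primary, which would multiply the error further. T4 is named as primary repeatedly; T3 and T5 are only to be estimated, and no statement makes a result there a primary success. A reader might also infer that a group-by-time interaction cannot test the hypothesis. That is true of an overall interaction restricted to T3–T5, which would miss a constant benefit. But the sample size section places the interaction at T4 and the time factor starts at T1, when the app is only being handed over. A T4-versus-T1 contrast would be a fair test of maintenance; the article just does not specify it.

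**Conclusion.** The point holds. T4 is fixed, but the article contradicts itself on the component and does not say which effect is decisive or was powered. If either component at T4 counts as success, the false-positive rate is up to about 10%: 9.75% under independence, with a range of 5% to 10% over all dependence. This rests on an either-component reading, which the text permits but does not state. The minutes part, as described, is not a comparison of the randomised groups; that conclusion needs no numerical assumption. The model form can still be chosen after the data are seen. The 72% power figure assumes that d = 0.35 applies to the baseline-adjusted T4 difference, a two-sided 5% test, and 15% dropout.

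**What to change.** Reconcile the abstract, the Primary outcome section, the sample size section and the Statistical analyses section around one confirmatory test: the group contrast at T4 in sport minutes per week over all randomised patients, with inactive patients counted as zero, adjusted for T0 minutes, two-sided at 5%.

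- Make active/inactive, T3, T5, overall main effects and other interactions secondary. If both components are to stay primary, state Holm or a fixed sequence.
- Fix the model for this test in advance. Report other transformations, links and the two-part model as sensitivity or secondary analyses.
- State which effect size the sample size refers to, and restate power for the named test.

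**Cost.** Visits and data collection do not change, but this is more than editing. Fewer results can be called primary. Demoting active/inactive changes the abstract's primary outcome after recruitment closed in December 2019, so the change should be dated, justified and made before outcome data are examined by group. The sample size can no longer be adapted. At d = 0.35 the named test has about 72% power rather than the stated 80%, and about 62% at Holm's first step if both components stay primary.

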**Discussion:**

This is the first evaluation of the effectiveness of an app in combination with a face-to-face group intervention to promote physical activity. The approach of using an app in addition to an effective face-to-face intervention program, both based on the MoVo model, might sustain positive intervention effects introduced in routine health care.

**Trial registration:**

The trial “A group- and smartphone-based psychological intervention to increase physical activity in patients with musculoskeletal conditions: A randomized controlled trial” is registered at the World Health Organization International Clinical Trials Registry Platform via the German Clinical Studies Trial Register (DRKS), DRKS00014814. Registered on 18 October 2018; URL: https://www.drks.de/drks_web/navigate.do?navigationId=trial.HTML&TRIAL_ID=DRKS00014814.

## Background

Musculoskeletal disorders such as chronic back pain, rheumatoid arthritis, and osteoporosis are highly prevalent conditions. The global prevalence of low back pain lasting longer than 1 month is estimated to be 23.2% [1]. The 1-year prevalence of back pain in Europe is 46.1%, and for neck and upper limb pain, it is 44.6% [2]. Furthermore, approximately 54 million (22.7%) of adults aged ≥18 years were diagnosed with arthritis in the United States between 2010 and 2012 [3]. In Germany, the prevalence rates of back pain and osteoarthritis are 22.5% and 20.6%, respectively, in people aged 20–75 [4]. Impairments of the musculoskeletal system cause high physical and economic burden to the individual and society [5, 6]. Low back pain, one of the most prevalent chronic musculoskeletal conditions, is the leading cause of years lived with disability worldwide, with other musculoskeletal conditions among the top ten causes [7].

Interventions to increase and maintain physical activity are among the most effective interventions for preventing further disease symptoms such as pain and dysfunction, and promoting health-related quality of life in patients with musculoskeletal disorders [5, 8–10]. An overview of systematic reviews found that exercise therapy yielded standardized mean differences between 0.30 and 0.65 for improving pain and function in individuals with different musculoskeletal conditions [5]. However, few patients manage to establish a stable level of physical activity behavior after inpatient treatment under their own volition [11, 12]. The Motivation-Volition concept for promoting Lifestyle-Integrated Sport Activity (MoVo-LISA; www.movo-konzept.de), a group-based intervention administered during inpatient rehabilitation, was developed to overcome low exercise adherence and to effectively promote long-term physical activity [13, 14]. Several randomized controlled trials (RCTs) (and quasi-experimental studies) have shown that MoVo-LISA has beneficial short- and long-term effects in patients with different conditions [15–19]. Promoting physical activity has consistently been shown to lead to a significant increase in exercise duration compared with preintervention or control group in psychosomatic [15], orthopedic [16, 17, 20], and cardiovascular [19] patients and in overweight or obese individuals [18]. In orthopedic patients, Fuchs and colleagues [16] reported the MoVo-LISA group as being more active than the usual care group by 28.5 min per week, even 12 months after discharge (per-protocol analyses). Moreover, investigations of treatment mediators strongly support the theoretical framework of the MoVo concept because behavior changes were shown to be based on changes in the underlying psychological factors [17, 21].

In previous studies, exercise duration measured after completion of MoVo-LISA was, on average, 156 min/week in the intervention group (IG). However, exercise duration decreased to 92 min/week at 6 months after discharge [13, 17]. New effective and cost-effective ways to prevent this decrease are needed. One way to do so could be to use technologies such as mobile applications (apps) to support participants in maintaining MoVo-LISA promoted habits and thus their level of physical activity. Several studies and systematic reviews with and without meta-analyses have shown that internet- and mobile app–based interventions can effectively and potentially cost-effectively increase and help maintain the amount of physical activity [12, 22–29]. A recent systematic review reported significant health improvements of app-based interventions targeting at physical activity in 14 of 21 studies [28].

Despite significant improvements, the positive effects of mobile apps have not been consistently reported, particularly in studies that use apps as stand-alone interventions. This might be due to internet- and mobile app–based interventions battling with repeatedly high dropout rates [30–35]. In internet-delivered physical activity behavior change programs, the average cross-study attrition rate was 23% in the IGs (reported in 28 of 34 studies) [29]. This effect seems to be more pronounced in studies using apps as stand-alone interventions. There is also evidence that multicomponent interventions lead to higher efficacy in behavioral and health outcomes than interventions consisting of apps alone [28]. Thus, blended interventions combining both face-to-face sessions and mobile material might be less prone to suffer from high withdrawal. Another advantage of blended interventions is that they can increase therapy intensity, which in turn might increase intervention effects [36]. In a systematic review of blended face-to-face and internet-based interventions for the treatment of mental disorders in adults, Erbe and colleagues found that these interventions can be more effective than no treatment [37]. Thus, an app embedded within a face-to-face intervention might help maintain the increased amount of physical activity that was acquired in a face-to-face intervention. Therefore, we developed a smartphone app based on the MoVo concept (“MoVo-App”) and adapted it to the MoVo-LISA group intervention.

The following is the primary research question:
Can the combination of the face-to-face group-based intervention MoVo-LISA and MoVo-App increase maintenance of the initiated physical activity level in patients with musculoskeletal disorders more than MoVo-LISA without subsequent MoVo-App use?

We hypothesize that the additional MoVo-App can help to maintain the initiated level of physical activity (by the face-to-face group program) 6 months after clinic discharge in patients with musculoskeletal disorders more than MoVo-LISA without the app.

The following are secondary research questions:
2.Can the combination of MoVo-LISA and MoVo-App improve cognitive mediators of behavioral change (e.g., self-efficacy or action planning), and health-related variables (e.g., pain intensity, depression) in patients with musculoskeletal disorders more than the same face-to-face group-based intervention without subsequent MoVo-App use?3.Which cognitive and sociodemographic factors moderate and mediate the effects of MoVo-LISA and MoVo-App?

